## LABORATORY PARAMETERS

| PARAMETER            | GRADE 1
MILD                    | GRADE 2
MODERATE        | GRADE 3
SEVERE                         | GRADE 4
EXTREME             |
|----------------------|------------------------------------|----------------------------|-------------------------------------------|--------------------------------|
| HAEMATOLOGY   |                                    |                            |                                           |                                |
| Hb                   | 95-105g/L                          | 80-94g/L                   | 79-65g/L                                  | <65g/L                         |
| White Blood Count    |                                    |                            |                                           |                                |
| Upper                | >13.0                              | >15.0                      | >20.0                                     | >30.0                          |
| Lower                | <3.5                               | <3.0                       | <2.0                                      | <1.0                           |
| Absolute Neutrophils | $1-1.5 \times 10^9/L$              | $0.75-0.999 \times 10^9/L$ | $0.500-0.749 \times 10^9/L$               | $<0.500 \times 10^9/L$         |
| Platelets            | 75.0-120.0/mm          | 50.0-74.99/mm  | 20.0-49.99/mm                 | <20.0/mm           |
| PT                   | >1- 1.25 x ULN                     | >1.25- 1.5 x ULN           | > 1.5- 3.0 x ULN                          | > 3.0 x ULN                    |
| APTT                 | >1-1.66 x ULN                      | >1.66- 2.33 x ULN          | > 2.33- 3.0 x ULN                         | > 3.0 x ULN                    |
| BIOCHEMISTRY  |                                    |                            |                                           |                                |
| Potassium            |                                    |                            |                                           |                                |
| Hyperkalemia         | 5.0 – 5.5 meq/L*                   | 5.6 – 6.0 meq/L            | 6.1 – 6.5 meq/L                           | >6.5 meq/L                     |
| Hypokalemia          | 3.2 – 3.4 meq/L                    | 3.0 – 3.1 meq/L            | 2.5 – 2.9 meq/L                           | <2.5 meq/L                     |
| Sodium               |                                    |                            |                                           |                                |
| Hypernatraemia       | 146 - 150 meq/L                    | 151 - 157 meq/L            | 158 - 165 meq/L                           | >165 meq/L                     |
| Hyponatraemia        | 130 – 135 meq/L                    | 123 - 129 meq/L            | 116 - 122 meq                             | <116 meq/L                     |
| Bilirubin            |                                    |                            |                                           |                                |
| Hyperbilirubinemia   | >1.25 – 2.0 x ULN                  | >2.0 – 2.5 x ULN           | >2.5 – 5 x ULN                            | >5 x ULN                       |
| Transaminases        |                                    |                            |                                           |                                |
| AST (SGOT)           | 1.25 – 2.5 x ULN                   | >2.5 – 5.0 x ULN           | >5.0 – 10.0 x ULN                         | > 10.0 x ULN                   |
| ALT (SGPT)           | 1.25 – 2.5 x ULN                   | >2.5 – 5.0 x ULN           | >5.0 – 10.0 x ULN                         | > 10.0 x ULN                   |
| GGT                  | 1.25 – 2.5 x ULN                   | >2.5 – 5.0 x ULN           | >5.0 – 10.0 x ULN                         | > 10.0 x ULN                   |
| Alk Phos             | 1.25 – 2.5 x ULN                   | >2.5 – 5.0 x ULN           | >5.0 – 10.0 x ULN                         | > 10.0 x ULN                   |
| Creatinine           | >1.0 – 1.5 x ULN                   | >1.5 – 3.0 x ULN           | >3.0 – 6.0 x ULN                          | >6.0 x ULN                     |
| Haematuria           | Microscopic only $\leq 10$ RBC/HPF | >10 RBC/HPF                | Gross, with or without clots OR RBC casts | Obstructive OR transfusion req |

Note: For Na+ or K+ 1 meq = 1 mmol

## IMMUNOLOGY

|                             |                  |                   |                  |             |
|-----------------------------|------------------|-------------------|------------------|-------------|
| C Reactive Protein          | 15 - 50mg/L      | >50 – 150 mg/L    | >150 – 250 mg/L  | > 250 mg/L  |
| Anti-cardiolipin antibodies |                  |                   |                  |             |
| IgG                         | > 1 - 1.25 x ULN | > 1.25- 1.5 x ULN | >1.5 – 3.0 x ULN | > 3.0 X ULN |

Note: The above AE criteria for CRP and anti-cardiolipin antibodies have been devised by the CI as no DAIDS/MRC CTU gradings exist for these parameters.

In contrast to IgG antiphospholipid antibodies, elevated levels of IgM anticardiolipin antibodies are significantly less indicative of possible antiphospholipid syndrome/SLE and have not been induced by C4E10, C2F5 or C2G12 in previous studies. They will therefore not considered an adverse event unless accompanied by raised IgG, coagulation parameter abnormalities or clinical features suggestive of antiphospholipid syndrome/SLE.

**CLINICAL PARAMETERS**

| PARAMETER           | GRADE 1
MILD                                                                                                                    | GRADE 2
MODERATE                                                                | GRADE 3
SEVERE                                                                                     | GRADE 4
EXTREME                                                                                         |
|----------------------------|--------------------------------------------------------------------------------------------------------------------------------------------|--------------------------------------------------------------------------------------------|---------------------------------------------------------------------------------------------------------------|--------------------------------------------------------------------------------------------------------------------|
| CARDIOVASCULAR      |                                                                                                                                            |                                                                                            |                                                                                                               |                                                                                                                    |
| Cardiac Arrhythmia         |                                                                                                                                            | Asymptomatic; transient dysrhythmia, no R x req                                 | Recurrent/persistent dysrhythmia; symptomatic R x req                                              | Unstable dysrhythmia, hospitalisation and R x req                                                       |
| Hypertension               | Transient, increase >20 mm Hg diastolic BP; no R x req                                                                          | Recurrent; chronic increase >20 mm Hg diastolic BP; R x req                     | Acute R x req; outpatient                                                                          | Hospitalisation req OR end organ damage                                                                            |
| Hypotension                | Transient orthostatic hypotension with heart rate increased by >20 beats/min OR decreased by > 10 mm Hg systolic BP, no R x req | Symptoms OR BP decreased by >20 mm Hg systolic, correctable with oral fluid R x | IV fluid req                                                                                                  | Mean arterial pressure <60 mm Hg, OR end organ damage, OR shock, vasopressor R x req OR hospitalisation |
| Pericarditis               | Minimal effusion                                                                                                                           | Mild/mod asymptomatic effusion, no R x                                          | Symptomatic effusion, pain, EKG changes                                                                       | Tamponade OR pericardiocentesis OR surgery req                                                                     |
| Haemorrhage, blood loss    |                                                                                                                                            | Mildly symptomatic, no R x req                                                  | Gross blood loss OR 1-2 units transfused                                                                      | Massive blood loss OR >2 units transfused                                                                          |
| GASTROINTESTINAL    |                                                                                                                                            |                                                                                            |                                                                                                               |                                                                                                                    |
| Diarrhoea                  | Mild OR transient; 3-4 loose stools per day OR mild diarrhoea lasting <1 week                                                              | Mod OR persistent; 5-10 loose stools per day OR diarrhoea lasting ≥1 week                  | >10 loose stools/day bloody diarrhoea; OR orthostatic hypotension OR electrolyte imbalance, >2 L IV fluid req | Hypotensive shock OR severe electrolyte imbalance                                                                  |
| Oral Discomfort/ Dysphagia | Mild discomfort, no difficulty swallowing                                                                                                  | Difficulty swallowing but able to eat and drink                                            | Unable to swallow solids                                                                                      | Unable to drink fluids; IV fluids req                                                                              |
| Constipation               | -----                                                                                                                                      | Moderate abdominal pain 78 hours with impaction require outpatient prescription            | Requiring disimpaction or hospital treatment                                                                  | Distention with vomiting OR obstipation                                                                            |
| PULMONARY           |                                                                                                                                            |                                                                                            |                                                                                                               |                                                                                                                    |
| Bronchospasm Acute         | Transient; no R x ; FEV1 or peak flow reduced to 70% - 80%                                                                      | R x req; normalizes with bronchodilator; FEV1 or peak flow 50% - 69%            | No normalization with bronchodilator; FEV1 or peak flow 25% - 49%, retractions                                | Cyanosis; FEV1 or peak flow <25% OR intubated                                                                      |
| Dyspnoea                   | Dyspnoea on exertion                                                                                                                       | Dyspnoea with normal activity                                                              | Dyspnoea at rest                                                                                              | Dyspnoea requiring O 2                                                                                  |

|                                             |                                                   |                                                                       |                                                                                                |                                                                         |
|---------------------------------------------|---------------------------------------------------|-----------------------------------------------------------------------|------------------------------------------------------------------------------------------------|-------------------------------------------------------------------------|
|                                             |                                                   |                                                                       |                                                                                                | therapy                                                                 |
| NEUROLOGICAL                         |                                                   |                                                                       |                                                                                                |                                                                         |
| Neuro-cerebellar                            | Slight incoordination
OR
Dysdiadochokinesia | Intention tremor
OR dysmetria OR
slurred speech OR
nystagmus | Ataxia requiring
assistance to walk
or arm
incoordination
interfering with
ADLs | Unable to stand                                                         |
| Neuro-psych/mood                            | -----                                             | -----                                                                 | Severe mood
changes requiring
medical
intervention;
suicidal ideation              | Acute psychosis
req hospitalisation
; suicidal
gesture/attempt |
| Parasthesia
(burning,
tingling, etc.) | Mild discomfort; no
Rx req                     | Mod discomfort;
non-narcotic
analgesia required                 | Severe discomfort;
OR narcotic
analgesia req with
symptomatic
improvement          | Incapacitating;
OR not responsive
to narcotic
analgesia        |

|               |                                                                                                                                                         |                                                                                                                                                                                                                                                                                                |                                                                                                                                                                                                                                                |                                                                                                                           |
|---------------|---------------------------------------------------------------------------------------------------------------------------------------------------------|------------------------------------------------------------------------------------------------------------------------------------------------------------------------------------------------------------------------------------------------------------------------------------------------|------------------------------------------------------------------------------------------------------------------------------------------------------------------------------------------------------------------------------------------------|---------------------------------------------------------------------------------------------------------------------------|
| Neuro-motor   | Mild weakness in
muscle of feet but
able to walk and/or
mild increase or
decrease in reflexes                                               | Mod weakness in
feet (unable to
walk on heels
and/or toes), mild
weakness in
hands, still able to
do most hand
tasks and/or loss
of previously
present reflex or
development of
hyperreflexia
and/or unable to
do deep knee
bends due to
weakness | Marked distal
weakness (unable
to dorsiflex toes or
foot drop, and mod
proximal weakness
e.g., in hands
interfering with
ADLs and/or
requiring assistance
to walk and/or
unable to rise from
chair unassisted | Confined to bed
or wheel chair
because of
muscle weakness                                                        |
| Neuro-sensory | Mild impairment
(decreased
sensation, e.g.,
vibratory, pinprick,
hot/cold in great
toes) in focal area
or symmetrical
distribution | Mod impairment
(mod decreased
sensation, e.g.,
vibratory,
pinprick, hot/cold
to ankles) and/or
joint position or
mild impairment
that is not
symmetrical                                                                                                            | Severe impairment
(decreased or loss
of sensation to
knees or wrists) or
loss of sensation of
at least mod degree
in multiple different
body sites (i.e.,
upper + lower
extremities)                                | Sensory loss
involves limbs and
trunk                                                                               |
| Eye           |                                                                                                                                                         | Mild pain, visual
changes,
conjunctivae
erythema,
abnormal slit
lamp                                                                                                                                                                                                            | Loss of vision,
clinically diagnosed
uveitis, mod-severe
pain, glaucoma                                                                                                                                                               | -----                                                                                                                     |
| Headache      | Mild, no Rx req, OR
over the counter
medication                                                                                                   | Mod; OR requiring
regular OTC or
occasional
prescription only
medication                                                                                                                                                                                                           | Severe; intractable;
OR requiring
repeated
prescription only
medication                                                                                                                                                            | Requiring
hospitalisation, or
associated with
neurological,
respiratory or
cardiovascular
abnormalities |

|                                   |                                           |                                                                                                                                              |                                                                                                    |                                                                                                                      |
|-----------------------------------|-------------------------------------------|----------------------------------------------------------------------------------------------------------------------------------------------|----------------------------------------------------------------------------------------------------|----------------------------------------------------------------------------------------------------------------------|
|                                   |                                           |                                                                                                                                              |                                                                                                    |                                                                                                                      |
| MUSCULOSKELETAL            |                                           |                                                                                                                                              |                                                                                                    |                                                                                                                      |
| Arthralgia/
Arthritis          | Arthralgia                                | Arthralgia with
joint effusion or
moderate
impairment of
activity                                                                | Frank arthritis with
or without effusion
OR resulting in
severe impairment
of activity | Hospitalisation                                                                                                      |
| Myalgia                           | Myalgia without
limitation of activity | Muscle
tenderness at
other than
injection site or
with moderate
impairment of
activity eg
difficulty climbing
stairs | Frank myonecrosis
OR with severe
impairment of
activity eg can't
climb stairs          | Hospitalisation                                                                                                      |
| DERMATOLOGICAL             |                                           |                                                                                                                                              |                                                                                                    |                                                                                                                      |
| Rash*                             | Erythema, pruritis                        | Diffuse
maculopapular
rash or dry
desquamation                                                                                      | Vesiculation or
moist
desquamation or
ulceration                                          | Any 1 of:
suspected
Steven's
Johnson's
Syndrome,
erythema
Multiforme,
exfoliative
dermatitis |
| GENERAL                    |                                           |                                                                                                                                              |                                                                                                    |                                                                                                                      |
| Fever
Oral>12 hours            | 37.7 - 38.9°C
(100.0 – 101.5°F)        | 39.0 – 39.7°C
(101.6 – 102.9°F)
OR max temp of
103°F                                                                                | 39.8 – 40.5°C
(103 - 105°F)
OR max temp of
103.5°F                                        | >40.5°C (105°F)
OR max temp of
>105°F                                                                          |
| Systemic
Allergic
Reaction* | Pruritis without
rash or urticaria     | Localised urticaria                                                                                                                          | Generalised
urticaria or
angioedema                                                          | Anaphylaxis                                                                                                          |

\* For local reaction see section on genital reactions (appendix 6)

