#### 5.5.2 Secondary endpoints:

- 24 hours post-1st dose, and 36 hours post-12th dose cervico-vaginal lavage MAb levels
- 24 hours post-1st dose, and 36 hours post-12th dose Mab levels in self-sampled vaginal aspirate
- 8 hours post-1st dose, and 12 hours post-12th dose serum MAb levels
- Number of grade 3 or above genital adverse events (see Appendix 6) during the dosing or follow up period
- Number of grade 3 or above other clinical or laboratory adverse (see Appendix 7) events confirmed at examination or on repeat testing respectively during the dosing or follow up period
- Number of events attributable to the study gel leading to discontinuation of gel

Data on local events listed above will be solicited with specific questions and/or cervico-vaginal and colposcopic examination. Data on laboratory events will be collected through the routine tests or in response to a clinical event. Data on other events will be collected with open questions. Detail on the analysis of MAbs in vaginal secretions and serum samples can be found in section 10.4.

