### **9.4.1 Interruption of dosing**

Interruption of dosing describes a temporary cessation of study gel use. Interruption of dosing will occur in the presence of:

- a grade 2 or above solicited genital adverse event
- any clinical event at the discretion of the CI which should lead to discontinuation of study gel

Dosing may be recommenced after interruption following an adverse event at the discretion of the CI.

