### **9.4.2 Discontinuation of dosing**

Discontinuation of dosing describes a permanent cessation of study gel use. Discontinuation of dosing will occur in the presence of:

- a grade 3 or above solicited genital adverse event
- a grade 3 or above clinical or laboratory event
- any clinical event at the discretion of the CI which should lead to discontinuation of study gel

Interruption or discontinuation of gel use may also occur if the participant desires to stop study gel use. Wherever possible, participants who discontinue study gel use either by choice or following advice will continue to adhere to the follow up schedule up to the final visit.

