## **9.5 Temporarily halting or stopping the study**

In the case of 3 women experiencing either a grade 3 or above genital adverse event or grade 3 or above clinical or laboratory adverse event, the study will be temporarily halted pending unblinded review by the Data Monitoring Committee (DMC). Several severe or

serious AEs, which are probable in relation to the study gel, will lead to the study being terminated at that point. The decision to stop the study rests on the CI, with recommendations from the DMC (see section 11.6.3).

The Sponsor reserves the right to terminate the study at any time.

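### Appendix 7 fever row: Fahrenheit figures at two grade boundaries do not match the Celsius figures, so a sustained fever of 39.5–39.7 °C is grade 2 on one scale and grade 3 on the other (minor)

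*Protocol*

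**What the plan says.** The row is in the clinical parameters table of Appendix 7 and is labelled "Fever Oral>12 hours". Its first three grades are:

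- Grade 1: "37.7 - 38.9°C (100.0 – 101.5°F", with no peak clause.
- Grade 2: "39.0 – 39.7°C (101.6 – 102.9°F) OR max temp of 103°F".
- Grade 3: "39.8 – 40.5°C (103 - 105°F) OR max temp of 103.5°F".

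Grade 4 starts above 40.5 °C, with 105 °F in brackets, or at a peak above 105 °F. The appendix does not say which scale governs if the two differ.

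Three rules in the protocol use the grade 3 line for clinical events:

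- Section 9.4.2 makes gel discontinuation follow from "a grade 3 or above clinical or laboratory event".
- Section 9.5 provides that once three women have had a grade 3 genital event or a "grade 3 or above clinical or laboratory adverse event, the study will be temporarily halted pending unblinded review" by the Data Monitoring Committee follows.
- Section 5.5.2 lists as a secondary endpoint the "Number of grade 3 or above other clinical or laboratory adverse (see Appendix 7) events confirmed at examination or on repeat testing respectively".

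The automatic rule at grade 2, in section 9.4.1, is confined to "a grade 2 or above solicited genital adverse event".

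**The concern.** A grading table with two scales should give the same grade whichever scale is read. Here the Celsius bands run on from one another without a gap, but the bracketed Fahrenheit limits at two boundaries are not their equivalents. At the grade 2/3 boundary the choice of scale decides whether a woman stops gel permanently, whether she is one of the three needed to halt the study, and whether a confirmed event enters a comparison between arms.

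The peak clauses make the row harder to apply. A temperature of 103 °F is a grade 2 peak and also the bottom of the grade 3 band, while the grade 3 peak is 103.5 °F. The row therefore offers two Fahrenheit starting points for grade 3. The label suggests that the bands are for fever lasting more than 12 hours and the peaks for any duration, but the row does not say so.

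**Working it through.** **Inputs.** All limits come from the fever row of Appendix 7.

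**Formulas.** °F = 1.8 × °C + 32, and °C = (°F − 32) / 1.8.

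**Step 1: convert each printed Celsius limit and compare it with the figure beside it.**

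| Limit | °C printed | Converted °F | °F printed | Printed − converted |
|---|---|---|---|---|
| Grade 1 lower | 37.7 | 99.86 | 100.0 | +0.14 |
| Grade 1 upper | 38.9 | 102.02 | 101.5 | −0.52 |
| Grade 2 lower | 39.0 | 102.20 | 101.6 | −0.60 |
| Grade 2 upper | 39.7 | 103.46 | 102.9 | −0.56 |
| Grade 3 lower | 39.8 | 103.64 | 103 | −0.64 |
| Grade 3 upper / grade 4 | 40.5 | 104.90 | 105 | +0.10 |

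The first and last lines reproduce the printed figure within rounding. The four in the middle do not. Four printed figures are off, at two boundaries.

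**Step 2: convert back.** 101.5 °F = 38.61 °C, 101.6 °F = 38.67 °C, 102.9 °F = 39.39 °C and 103 °F = 39.44 °C. The Fahrenheit boundaries therefore lie 0.29 to 0.36 °C below the Celsius ones.

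**Step 3: grade each 0.1 °C reading on both scales, with °F rounded to one decimal.**

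- Grade 1 by Celsius has 13 readings (37.7 to 38.9). Three become grade 2 by Fahrenheit: 38.7 (101.66 °F), 38.8 (101.84 °F) and 38.9 (102.02 °F). The reading below them, 38.6 °C = 101.48 °F, stays grade 1.
- Grade 2 by Celsius has 8 readings (39.0 to 39.7). Three become grade 3 by Fahrenheit: 39.5 (103.10 °F), 39.6 (103.28 °F) and 39.7 (103.46 °F). The reading below them, 39.4 °C = 102.92 °F, stays grade 2.
- Grade 3 by Celsius has 8 readings (39.8 to 40.5, that is 103.64 to 104.90 °F). None changes grade.

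**Step 4: the peak clauses.** The grade 2 peak, 103 °F, is 39.44 °C and lies inside the Celsius grade 2 band. The grade 3 peak, 103.5 °F, is 39.72 °C, at the Celsius grade 2/3 line. The peaks therefore sit close to the Celsius bands and not to the bracketed 103 °F floor of grade 3. If a short fever is judged by its peak alone, only 39.7 °C is doubtful: 103.46 °F falls short of 103.5 °F but rounds to it. For a fever over 12 hours the band conflict in Step 3 remains.

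**Step 5: consequences.** At grade 2/3, sections 9.4.2, 9.5 and 5.5.2 all apply, and one fever graded up would supply one of the three women needed for a halt. At grade 1/2 nothing is automatic, because fever is not among the solicited genital events in Appendix 6. The comparisons in section 10.2.2 use grade 3 or above, all events, or related events, so grade 1 against grade 2 alters none of them.

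**The case against.** The strongest reply is that no one at this site need be misled. Celsius comes first and Fahrenheit is in brackets, as a secondary equivalent usually is, and all visits are at one UK hospital (section 5.1). Nothing in the protocol shows that Fahrenheit is used. Read in Celsius, the bands are sound and the peaks nearly fit. The overlap at 103 °F also compares a band, apparently for sustained fever, with a peak, and taking the higher grade is an obvious reading.

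The exposure is small too. Table 7-1 has no temperature line and places physical examination only at visits 1 and 8. Appendix 8 makes the diary card source data only for the time of home dosing. The endpoint needs confirmation at examination, and the halt is temporary and leads to a review.

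Most of this stands and limits the weight of the point. It does not make the row correct. No text says that Celsius governs, the peak clauses exist only in Fahrenheit, and a sustained 103 °F meets both the grade 2 and the grade 3 cell with no rule to choose between them.

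A reader might infer more than the documents support:

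- **That severe fever would be missed.** Measured against the Celsius bands, the Fahrenheit figures are stricter at both disputed boundaries, so using them over-grades.
- **That the Fahrenheit figures are known to be the mistaken ones.** Appendix 7 says that its scales are based on outside grading systems not reproduced in the protocol. Had 103 °F (39.4 °C) been intended, it would be the Celsius limit that under-grades 39.5 to 39.7 °C. This is why the limit needs clinical confirmation.
- **That the grade 1/2 mismatch affects dosing.** No automatic rule attaches to a grade 2 fever.

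**Conclusion.** The point holds as a minor correction. The grade 2/3 boundary is the one that matters, because three of the eight 0.1 °C readings in the Celsius grade 2 band become grade 3 on the Fahrenheit scale. The grade 1/2 mismatch is the same kind of slip and changes only the recorded grade.

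The band finding rests on exact unit conversion, with differences of up to 0.14 °F treated as rounding. The consequence rests on two conditions: that someone grades from the bracketed figures, and that a fever in this narrow range is reported or found in one of 30 healthy women. The protocol gives no fever rate, so I put no probability on it. No pharmacokinetic result is affected.

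**What to change.** 1. The clinical team confirms the intended grade 3 limit. The Celsius bands are listed first and are contiguous, so 39.8 °C is the natural default. It is the less strict of the two limits, so it should be a stated clinical choice.
2. Print the row on that one scale and delete or correct the bracketed equivalents. If Celsius is kept, the correct equivalents are 99.9–102.0, 102.2–103.5 and 103.6–104.9 °F for grades 1 to 3, and above 104.9 °F for grade 4.
3. State whether the 12-hour condition applies to the bands.
4. Delete the peak clauses, or restate them on the same scale so that they fit the bands. With the Celsius default that gives 39.4–39.7 °C for grade 2 (103 °F = 39.4 °C), 39.8–40.5 °C for grade 3 and above 40.5 °C for grade 4. Deletion is simpler, because a restated grade 3 peak equals the band and serves only for fevers shorter than 12 hours.
5. Recheck any fever already graded, blind to arm.

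The cost is a corrected appendix page and that recheck. No new procedure, visit or sample is needed.
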